#### Implementation for CSC staff

CSC stroke teams will receive study specific training about use of the intervention pathway and remote specialist assessment.

### Study population

Although by its nature the pathway is only intended for use with *some* suspected stroke patients (see also ‘Study intervention’ above), deployment of the pathway is likely to have wider impacts for stroke services across ambulance regions serving PSCs and CSCs. The study will examine outcomes within several analysis populations to report both the impact on the population eligible to receive the pathway and subsequent thrombectomy, and other populations where effects may also be seen. The overall study population comprises patients where:

an ambulance practitioner from a randomised station/team attends the incident.conveyance is to a PSC which refers patients to the participating CSC, or, directly to the participating CSC (ie, the incident is in either a secondary transfer area or an area where the CSC is accessed directly).acute stroke is suspected by the attending ambulance practitioner (ie, FAST positive or any observed new focal neurological symptoms which indicate acute stroke according to the ambulance practitioner’s clinical judgement) OR acute stroke was diagnosed following arrival at a participating PSC or CSC irrespective of ambulance practitioner initial judgement of symptom cause.

The important ‘sub’ populations which will be used to examine the impacts of the SPEEDY pathway are as follows:

Ambulance suspected acute stroke: ‘Ambulance suspected acute stroke population’.Ambulance suspected stroke demonstrating pathway clinical criteria, assessed within the agreed time window for the relevant region and usual conveyance would be to a PSC: ‘Target population’.Ambulance suspected stroke demonstrating pathway clinical criteria, assessed within the agreed time window for the relevant region and usual conveyance would be to a PSC, plus, following hospital assessment, a diagnosis of ischaemic stroke is assigned: ‘***Primary analysis population***’.

The population selected for the primary analysis reflects the group where direct effects of the intervention can be evaluated, ie, the population eligible for both pathway deployment and subsequent thrombectomy treatment.

All populations are illustrated in figure 2.

**Figure 2 F2:**
[figure not shown]
Study populations.

### Participant enrolment

In keeping with previous cluster randomised health service trials,^30^ a waiver of individual patient consent was granted for participant enrolment and data collection for this trial. This approach was proposed and justified for the reasons outlined below. Note that enrolment for the process evaluation is a separate procedure and detail is provided in ‘Process evaluation’ below.

Thrombectomy for acute stroke is a National Institute for Health and Care Excellence (NICE) recommended treatment commissioned by NHS England, with suboptimal delivery in most regions. The study intervention does not change clinical eligibility for thrombectomy or reallocate treatment decision responsibility but aims to facilitate access to the procedure for patients that meet the established treatment criteria.The study intervention pathway carries negligible risk of harm whether or not direct CSC admission is accepted or declined. Where direct CSC admission is declined, patients will still be conveyed urgently to the local PSC and undergo emergency stroke assessment. If following a PSC assessment, suitability for thrombectomy is confirmed, a secondary transfer will occur in keeping with standard care. Where direct CSC admission is accepted, the transfer will be monitored by ambulance practitioners who will respond to any changes in patient status as per usual care. If, following arrival, thrombectomy is judged not to be appropriate, the medical team will still provide all treatments required.All data required for the study can be obtained from routinely recorded clinical service data; there is no burden on patients for research visits (see also ‘Data collection’ below).Obtaining consent from patients who have any part of the pathway deployed, corresponding standard care patients, or the full study population would be very challenging and render the research impractical or bias:Suspected stroke is a time-critical condition and introducing consent during ambulance assessment would be unacceptable due to delays to care.Although consent could potentially be deferred until emergency assessments have been completed at hospital, there is no routine linkage of ambulance recorded data to hospital data to enable hospital research staff to identify eligible patients. An incomplete and bias study population would result due to failure to identify all relevant patients.Deferred hospital consent is also not straightforward as effects of suspected stroke/confirmed stroke can result in a lack of mental capacity, communication difficulties and early mortality. The previous experience of the study investigator team is that complicated consent processes also result in incomplete enrolment of eligible patients and risk a bias sample. In particular, patients suitable for thrombectomy treatment, the target of the study intervention, are often the most seriously affected by stroke and consequently the most likely not to be enrolled if consent were required.Each NHS stroke centre assesses approximately 5–10 suspected stroke patients per day, and the previous experience of the study investigator team is that consent processes for this volume of patients are not practical, further adding to the risk of an incomplete and bias sample.Following emergency assessment at hospital, suspected stroke/confirmed stroke patients can be located in multiple different wards or indeed rapidly discharged or transferred to a different hospital site, additionally hindering attempts at consent and resulting in lack of enrolment.

### Data collection

Other than data describing delivery of the intervention pathway, all data required for analysis and reporting of the cluster trial (including health economic evaluation) are routinely collected by ambulance or hospital services. In addition, data required at the hospital level for patients with a diagnosis of stroke are provided to the Sentinel Stroke National Audit Programme (SSNAP).^11^

Three methods of data collection are being used to generate four datasets which require linkage.

Table 1 summarises the data required for the study, the routine location of these data and the data collection method. The online supplemental file lists the data items obtained in each dataset.

**Table 1 T1:** Study data required, routine location and data collection method

Data required for the study	Routine location of data	Data collection for this study
Ambulance assessment parameters and care process information for patients suspected to be stroke by the attending ambulance practitioner and conveyed to a study CSC or feeding PSC.	Ambulance service	Data provided from participating ambulance services via regular exports from their existing electronic routine care records. Data requested will be for patients where stroke was suspected by an ambulance practitioner and the patient was conveyed to a study CSC or feeding PSC.
Hospital categorised diagnosis for patients who were suspected to be stroke by the attending ambulance practitioner and conveyed to a study CSC or feeding PSC. Diagnosis categorised as: ischaemic stroke haemorrhagic stroke non-stroke mimic condition	First admission hospital (PSC or CSC) SSNAP if a diagnosis of stroke is assigned	Data provided from SSNAP via regular exports of their dataset. Data requested will be for patients admitted by ambulance to study CSCs or feeding PSCs. SSNAP does not contain data from patients diagnosed with non-stroke mimic conditions and therefore this diagnostic category will be assumed for patients within the ambulance dataset who do not have a matching SSNAP record.
Hospital categorised diagnosis for patients who were *not *suspected to be stroke by the attending ambulance practitioner and conveyed to a study CSC or feeding PSC. Diagnosis categorised as: ischaemic stroke haemorrhagic stroke	First admission hospital (PSC or CSC) SSNAP	Data provided from SSNAP via regular exports of their dataset. Data requested will be as above.
Clinical characteristics and care received at hospital for patients with a diagnosis of stroke and conveyed to hospital by ambulance.	First admission hospital (PSC or CSC) SSNAP	Data provided from SSNAP via regular exports of their dataset. Data requested will be as above.
Thrombectomy treatment parameters for patients conveyed to hospital by ambulance (if received).	CSC	Data provided from participating CSCs via a standard research ‘case record form’. The case record form exists in paper and electronic formats (secure online study database) and data are collected contemporaneously for each patient who receives thrombectomy. All data are added to the online database either directly or from the initial paper record, according to CSC preference. This research-specific data collection form is called: ‘CSC thrombectomy treatment log’.
Study intervention pathway ‘SPEEDY pathway’ content (if received)	CSC	Data provided from participating CSCs via a standard research ‘case record form’. A paper case record form is completed contemporaneously for each call from an ambulance practitioner activating the intervention pathway. The data from the paper form is subsequently uploaded into the online study database. This research-specific data collection form is called: ‘CSC SPEEDY call log’.

CSC, comprehensive stroke centre; PSC, primary stroke centre; SPEEDY, Specialist PrE-hospital rEDirection for ischaemic stroke thrombectomY; SSNAP, Sentinel Stroke National Audit Programme.

#### Data linkage

Because of the nature of the study, some patients will NOT link across all datasets. For example, an ambulance suspected stroke case which receives a non-stroke mimic diagnosis following hospital assessment will not have a SSNAP record because SSNAP only obtains data on stroke cases. All data are required for analyses, not solely data from patients who link across every dataset.

Figure 3 summarises the study datasets and linkage.

**Figure 3 F3:**
[figure not shown]
Study datasets and linkage. CSC, comprehensive stroke centres; PSC, primary stroke centre; SPEEDY, Specialist PrE-hospital rEDirection for ischaemic stroke thrombectomY; SSNAP, Sentinel Stroke National Audit Programme.

Linkage is centralised at the study co-ordinating centre at Newcastle University, England. Identifiable patient information is not sought and instead the main data items being used for linkage are:

first admission hospital name.first admission hospital arrival date and time.month and year of date of birth (or age if date of birth is unknown).gender.

#### Assignment of randomisation group

All patients will be assigned to a randomisation group according to the allocation of the attending ambulance practitioner. The ambulance data exports contain information on attending practitioners and/or stations/teams such that randomisation group can be assigned. For patients in the full study population where ambulance practitioners did not suspect stroke and this was diagnosed only after arrival at hospital, information on attending practitioners (or station/team) will be sourced in arrears from the relevant ambulance service.

### Blinding

Due to the nature of the study intervention, it is not possible to blind intervention ambulance practitioners or receiving hospital stroke teams. However, because the study is cluster randomised, staff cannot influence group allocation or select patients for inclusion in the trial; all patients who meet the eligibility criteria will be included and assigned to a study group based on the randomisation allocation of the attending ambulance practitioner. Patients seen by intervention group ambulance practitioners will be included in the study whether or not the intervention pathway was deployed, and whether or not thrombectomy was received.

Participating sites are asked to conceal study group information from the clinician performing thrombectomy, which should be possible because NHS neuroradiologists are not routinely involved in urgent arrival care processes. Thrombectomy treatment decisions are based on clinical details conveyed via the hospital stroke team and brain imaging appearances. CSCs already receive patients from outside their immediate area through standard (secondary transfer) care and therefore information about a patient’s original locality would not by itself cause unblinding.

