*A remote specialist assessment* undertaken by a member of the CSC team to make a decision about whether the patient should be redirected to the CSC or continue to the local PSC.

This assessment involves initial use of a checklist to confirm pathway eligibility (ie, routine conveyance would be to a PSC, FAST results, symptom onset time, AVPU score) and record additional clinical characteristics including key vital signs required to inform a decision about the likely appropriateness of thrombectomy. Thereafter, CSC staff will seek extra information as required which may influence the destination choice. A decision about direct admission to the CSC or to continue to the local PSC is subsequently made.

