### Implementation of the study intervention and control

#### Implementation for ambulance practitioners

Any grade of ambulance practitioner based within a randomised station/team that would normally attempt to identify suspected stroke is involved in the study.

When the study launches in each region, intervention ambulance practitioners are provided with information about the trial including pocket-sized cards covering pathway initiation criteria and specific contact details for the participating CSC team. The pathway was purposely designed to use routinely available information and as such negate a need for trial-specific training. Practitioners are instructed to start using the intervention pathway on a specific date in synchronisation with the receiving CSC.

Ambulance practitioners based within standard care stations are informed that a study about thrombectomy is taking place and routinely recorded data will be used, but otherwise instructed to continue with standard care pathways.

As double-crewed ambulances are typically dispatched to suspected stroke patients, it is expected that two ambulance practitioners will attend most incidents. Whilst typically this should be two practitioners from the same station/team and therefore the same randomisation allocation, there may be occasions when this is not the case and both an intervention and a control practitioner are in attendance. In this latter situation, the patient is considered allocated to the intervention group and the ambulance practitioners have been advised that the intervention pathway should take precedent.

During the duration of the trial, it is anticipated that the ambulance practitioner workforce within each region will be subject to change, ie, some practitioners will leave the service and new employees will commence. Because the study population comprises all suspected and confirmed strokes seen by randomised ambulance practitioners across a participating region, newly employed ambulance practitioners will become involved in the study when they commence their employment. If practitioners employed after study launch were excluded from involvement, the study population would be incomplete. New employees will be provided with details about the study in keeping with their allocated station.

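### The assurance that staff cannot select patients does not extend to the primary analysis population, whose entry depends on crew findings made after allocation; the no-match rule can also drop treated patients

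*Protocol article*

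**What the plan says.** All references are to the protocol article.

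- **Blinding.** The section accepts that "it is not possible to blind intervention ambulance practitioners or receiving hospital stroke teams", but adds that "because the study is cluster randomised, staff cannot influence group allocation or select patients for inclusion in the trial".
- **Study population.** The primary analysis population is narrower than the trial population. Its ambulance-side condition is "Ambulance suspected stroke demonstrating pathway clinical criteria, assessed within the agreed time window for the relevant region and usual conveyance would be to a PSC". Its hospital-side condition is that "following hospital assessment, a diagnosis of ischaemic stroke is assigned".
- **Study intervention.** The clinical criteria are suspected stroke with FAST arm weakness and speech disturbance, onset or waking within 5 hours, and an AVPU level other than Unresponsive. The remote assessment at the comprehensive stroke centre (CSC) begins with "initial use of a checklist to confirm pathway eligibility".
- **Implementation for ambulance practitioners.** Intervention crews receive "pocket-sized cards covering pathway initiation criteria". Control crews are told only that a thrombectomy study is running and that they should carry on as usual.
- **Secondary analyses.** The intention-to-treat analysis of rate and time is done within the primary analysis population.
- **Data collection, Table 1.** The national stroke audit (SSNAP) holds no mimics, so "this diagnostic category will be assumed for patients within the ambulance dataset who do not have a matching SSNAP record". Under Data linkage, the main keys are first hospital, arrival date and time, month and year of birth (or age), and gender.

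**The concern.** Cluster randomisation fixes which arm a patient belongs to. It does not fix which patients are counted when counting depends on a judgement made after allocation. Here the crew decides whether stroke is suspected, and the crew's findings decide whether the criteria are met. A card listing those criteria, given to one arm only, could change how often they are looked for, recorded or rounded. The two arms of the primary analysis population could then hold different kinds of patient. A difference in thrombectomy rate or onset-to-treatment time could partly reflect who was counted. An intention-to-treat analysis in the same population would not correct this.

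The no-match rule is a second, separate route. A patient with ischaemic stroke whose ambulance record fails to link becomes a mimic and leaves the primary analysis population. Read literally, this applies even when the CSC thrombectomy log shows that the patient was treated.

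**Working it through.** **1. The plan's own figures (Sample size).** These are not in dispute and set the scale.

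- Time: difference 30 min, SD 120 min, one-sided 5%, 90% power. Unclustered total = 4 × 120² × (1.645 + 1.282)² / 30² = 548.1. With 150 clusters and ICC 0.01, N = 548.1 × [1 + (N/150 − 1) × 0.01], so N = 563.2. Stated: 564.
- Rate: 13.2% vs 21.6%, two-sided 5%, 90% power. Unclustered total 852; with the same design effect, 894.3. Stated: 894.
- Population: 564/0.216 = 2611 and 564/0.132 = 4273. Stated: 2600 to 4300.

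**2. Does the assurance reach each population?**

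| Population | Entry condition | Can crew judgement affect entry? |
|---|---|---|
| Full, confirmed strokes | Crew suspicion or hospital diagnosis | Hardly; unsuspected strokes are also taken in |
| Full, mimics | Crew suspicion only | Yes |
| Primary analysis population | Crew suspicion, crew-assessed criteria, hospital diagnosis | Yes, for the first two |

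There is room for the findings to vary. Study intervention gives ambulance-hospital agreement of kappa 0.77 (95% CI 0.55 to 0.99) for arm weakness and 0.69 (0.56 to 0.82) for speech.

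**3. How far could the rate move?** The documents give no differential-entry figures, so these are assumptions. Take no true effect and 13.2% in both arms.

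- One arm's analysed set lacks a fraction f of its eligible patients, all untreated. Its rate becomes 13.2/(1 − f).
- One arm gains a fraction f of extra untreated patients. Its rate becomes 13.2/(1 + f).

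| f | Rate if lost | Rate if gained | False two-sided 5% finding if lost, N = 2600 | Same, N = 4300 |
|---|---|---|---|---|
| 5% | 13.9% | 12.6% | 8% | 9% |
| 10% | 14.7% | 12.0% | 17% | 23% |
| 20% | 16.5% | 11.0% | 59% | 77% |

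The last two columns treat rate as a stand-alone test, with design effect 1 + (N/150 − 1) × 0.01. To imitate the full 8.4-point effect, f would have to be 1 − 13.2/21.6 = 39%.

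**4. Time to thrombectomy.** This outcome is tested first and uses treated patients only, so adding or losing untreated patients does not touch it. It is biased only if the mix of treated patients differs. The standard error at N = 564 is 120 × √(4 × 1.0276/564) = 10.2 min. An assumed spurious shift of 5, 10 or 15 min in the favourable direction raises the one-sided 5% error to about 12%, 25% or 43%.

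**5. The no-match rule.** Equal non-match in both arms gives no difference between arms. The following are again assumptions.

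- Only untreated strokes fail to match. The rate becomes 13.2/[13.2 + 86.8 × (1 − u)]. With u = 5% vs 10% this gives 13.8% vs 14.5% (a 0.7-point difference before rounding); with 10% vs 20%, 14.5% vs 16.0% (1.5 points).
- In one arm, 10% of treated and 2% of untreated patients fail to match: 13.2 × 0.90 / (13.2 × 0.90 + 86.8 × 0.98) = 12.3%, a fall of 0.9 points.

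**The case against.** **What stands.** Read literally, the Blinding sentence is about inclusion in the trial, and trial inclusion means the full study population. That population also takes in strokes the crew did not suspect, so for confirmed strokes the sentence is broadly right and needs qualifying, not deleting. FAST, onset time and conscious level are standard-care items in both arms, and the ischaemic stroke diagnosis is made by the hospital. The no-match rule is the same in both arms. Rate and time in other analysis populations are already listed as secondary outcomes, and the article discloses a data-quality concern.

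**Stronger readings that the documents do not support.**

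- *The CSC checklist feeds eligibility in the intervention arm only.* Table 1 takes ambulance assessment data from routine record exports and uses the call log for pathway content. Nothing says that the log defines the population.
- *The full study population is free of the problem.* Mimics enter it only through crew suspicion. It is also heavily diluted: 2600 to 4300 of about 80 000 is 3.3% to 5.4%.
- *Failed links eat into the 564 procedures.* Sample size says enrolment continues until 564 treated patients have data, so lost links lengthen enrolment.
- *A fully allocation-blind population could be built from data already requested.* Receiving hospital teams are unblinded too. Ambulance exports are requested for suspected stroke only; for unsuspected strokes the article mentions only practitioner or station details, obtained in arrears.

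**What does not rescue the plan.** The primary comparison and its intention-to-treat companion both sit in the crew-dependent population. The other planned populations are not targeted at this gap. How dataset conflicts are resolved could be left to the analysis plan, but the article does state the mimic rule, and without an exception.

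**Conclusion.** The concern holds as a risk. The assurance does not cover the primary analysis population, because entry depends on suspicion and criteria assessed after allocation by crews who, in the intervention arm, are unblinded and prompted by cards. The intention-to-treat analysis inherits this.

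Size and direction are unknown. Under the assumed 5% to 20% loss of untreated patients from one arm, the rate moves by 0.7 to 3.3 points against an 8.4-point target. That is too little to imitate the whole effect, but enough to inflate the error rate materially at the expected population size. For time, only a change in the mix of treated patients matters, and the documents give no basis for sizing it. A reader might infer that the arms will be unbalanced; the documents do not show that.

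The no-match rule is a separate and smaller point. As written it misclassifies a patient whose CSC log shows a thrombectomy. It biases the comparison only if match failure differs by arm. That is plausible, because redirection changes the first hospital used as a linkage key, but it is not shown.

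The primary analysis also drops intervention patients whose crew did not initiate the pathway or reach the CSC. That is a different selection issue and is not counted here.

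**What to change.** 1. **Qualify the Blinding sentence.** Say that it applies to allocation and to inclusion of confirmed strokes in the full study population, and that it does not extend to the primary analysis population.
2. **Add a supportive intention-to-treat analysis of both co-primary outcomes.** Use ambulance-suspected patients with hospital-diagnosed ischaemic stroke, in the secondary-transfer area and the operating window, with onset within 5 hours by hospital record where available, whatever the crew recorded for FAST and AVPU. Compare by arm the proportion of these patients who enter the primary analysis population.
3. **Amend the no-match rule.** Do not class a non-match as a mimic when a CSC thrombectomy log or call log entry shows otherwise. Class the remaining uncertain non-matches as unlinked in a sensitivity analysis, and report linkage by arm.

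**Cost.** One further analysis population, some added linkage work and a few tables. The supportive population is more diluted than the primary one, still rests on crew suspicion and is not fully allocation-blind. Waking time may not be in the hospital record. It therefore serves as a check on the primary result and does not replace it.
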